## **5. DATA**

### **5.1 DATA COLLECTION AND HANDLING**

Data collection and entry onto a REDCap database, which will save data directly to UCL's data safe haven (DSH), will be undertaken at the individual sites. Cognition data will be collected via an excel spreadsheet (behavioural database) and stored on the DSH. Cleaning and analysis will be undertaken by N Worth using standard, secure, anonymous procedures for handling participant data. For further details, please refer to the Data Management Plan.

### **5.2 TIME POINTS OF OUTCOMES MEASURES**

Outcome measures are collected at baseline, 3 months and 6 months post-randomisation. Appendix 1 contains a list of all data collected during the study.

The primary outcome is participant-reported goal attainment at 3 months post-randomisation. This will also be collected as a secondary outcome at the 6 month post-randomisation follow up. This will be collected using the Bangor Goal Setting Interview (BGSi).

Secondary outcomes will be:

- Goal Satisfaction Scale ((using the Bangor Goal Setting Interview Scale)
- Cognitive function (tested using the cognitive batteries employed for Workstream 1)
- Quality of life (EQ-5D-5L)\*
- Life Space Assessment
- Social Functioning (SF-DEM)
- Instrumental Activities of Daily Living (IADL) Scale
- Generalised Anxiety Disorder Assessment (GAD-7)
- Patient Health Questionnaire (PHQ-8)
- Chalder Fatigue Scale
- Pittsburgh Sleep Quality (PSQI)
- DePaul Symptom Questionnaire – Post-Exertional Malaise (DSQ-PEM).
- Client Service Receipt Inventory (CSRI)\*

Cognitive function will be assessed using three complementary assessments (expanded below), to maximise understanding of cognition

- Cognitive function assessment 1 – battery of Cognitive tests
  - The Repeatable Battery for the Assessment of Neuropsychological Tests (RBANS)
  - The Delis-Kaplan Executive Function System: The Trail Making Test (Condition 2: Number Sequencing & Condition 4: Number-Letter Switching)
  - The Delis-Kaplan Executive Function System: Colour-Word Interference
  - The Delis-Kaplan Executive Function System: Phonemic Fluency
  - Wechsler Adult Intelligence Scale III: Digit Span
  - Test of Premorbid Functioning (TOPF)
- Cognitive function assessment 2 – online battery of cognitive tests
  - Gorilla
  - 4 Mountains (4MT)
- Cognitive function assessment 3
  - Neotiv suite

\*Health economic data not being analysed at by NWO.

### 5.3 DEFINITIONS AND CALCULATIONS OF OUTCOME MEASURES

For a full definition and respective calculations of each outcome measure please see Appendix 2.

### 5.4 SAFETY DATA

The number (and proportion) of participants experiencing AE/SAEs will be reported. No formal statistical testing will be undertaken of the safety data.

## 6. STATISTICAL ANALYSES

### 6.1 ANALYSIS TIME FRAME

**Table 1:** Summary of expected timelines for analysis

| TASK                 | EXPECTED DATE  |
|----------------------|----------------|
| Data Cleaning        | August 2024    |
| Data locking*        | August 2024    |
| Analysis completed** | September 2024 |

*\*The completion of data lock is dependent on the date of the final follow up, data entry from all sites, responses to data queries and sign off of the statistical analysis plan.*

*\*\*a minimum of 1 month between data lock and analysis report delivery is required.*

### 6.2 BASELINE ANALYSIS

A separate baseline analysis will not be conducted. A section of the main analysis and report will detail the characteristics of the study sample at baseline. Descriptive statistics will be used to describe the sample, see section 6.5.

### 6.3 INTERIM ANALYSIS

No interim analysis is planned.

### 6.4 PARTICIPANT FLOW AND CONSORT REPORTING

The patient flow information, as shown in Figure 2, as advised by CONSORT reporting standards, will be completed with values relating to participants numbers. Data will be presented on screening, eligibility, recruitment, treatment discontinuation and withdrawn/lost to follow up. Where possible reasons for ineligibility or non-recruitment will be reported. From these data related eligibility, recruitment and retention rates will be calculated and presented in the final analysis report.

[figure not shown]

**Figure 2:** Participant Flow diagram to be completed in line with CONSORT reporting guidelines.

## 6.5 DESCRIPTIVE STATISTICS

Descriptive statistics of the data will be presented. This will include randomisation figures, demographics, COVID19 data and outcome measure data along with completeness levels to assess missing data.

For all descriptive statistics continuous measures will be reported with mean values and standard deviations and categorical variables presented with counts and related percentages. If data are not normally distributed, then medians and interquartile ranges will be reported. Categorical variables will be reported with counts and related percentages. The following data will be presented:

- Participant demographics and sample characteristics
- Outcome measures at each timepoint (listed in section 5.2)
- Cognitive Assessments of cognitive function (listed in section 5.2)
- \*Intervention data summary; number of sessions attended.

*\*Presented in unblind report once all primary analysis listed in this SAP is complete.*

All data will be presented overall and split by allocation group.

## 6.6 ANALYSIS OF PRIMARY OUTCOME

The primary outcome, the BGSi (attainment score) at the 3 months, will be analysed using a multi-level (mixed effect) linear regression model to assess the differences between the two treatment arms. Stratification variables (Site) will be incorporated into the model as a random effect along with gender, age (continuous), years of education (continuous) and RBANS composite score at baseline as fixed factors. Baseline BGSi attainment score will also be incorporated to account for any differences at baseline.

The BGSi at 6 months will be analysed as a secondary outcome using the same model structure as the primary. Unadjusted (section 6.5) and adjusted results will be presented with associated 95% confidence intervals.

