| Funding                                            | NIHR                                                                                                                                                                                                                                                                                                                                                                                                                                                                                                                                                                                 |
| Other support                                      | Recruitment, testing, and rehab will be at the three clinical sites (Princess Royal Hospital Haywards Heath, Southampton Hospital, Greater Manchester Hospitals).
Statistical analyses will be done at the North Wales Clinical Trials Unit, Bangor. Health economic analyses will be done at the Centre for Health Economics and Medicines Evaluation, Bangor University.
Trial coordination is at the main clinical site under [name] (Princess Royal Hospital Haywards Heath).
MRI scanning will be done at the Clinical Imaging Sciences Centre, University of Sussex. |
| STORAGE of SAMPLES (if applicable)          | N/A                                                                                                                                                                                                                                                                                                                                                                                                                                                                                                                                                                                  |
| Human tissue samples                               | N/A                                                                                                                                                                                                                                                                                                                                                                                                                                                                                                                                                                                  |

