## 5 Experimental design and methods

### 5.1 Plan of investigation

#### 5.1.1 Participant recruitment

[figure not shown]

Figure 1. Trial flowchart including sample size

## Workstream 1

80 participants will be recruited from three clinical sites, namely the Cognitive Disorders Clinic, University Hospitals Sussex NHS Trust (PI [name]), representing one of the first clinics nationwide to offer a dedicated diagnostic and therapeutic service for cognitive Covid, Southampton General Hospital (PI [name]), and Greater Manchester Mental Health NHS Foundation Trust (PI [name]). As part of a substudy, 100 participants (60-70 with long Covid and 30-40 controls) will undergo MRI scanning at the University of Sussex.

Participants will be offered reimbursement of up to £20 for each study visit.

## Workstream 2

For the RCT 120 participants (for justification of this sample size, see power calculation below) will be recruited from the same clinics. If eligible participants in WS1 can take part in WS2.

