### **4.2 RANDOMISATION**

Randomisation will take place once consent and baseline data collection has been completed. Randomisation will be on a 1:1 allocation (intervention:control) via a secure online system hosted by NWOORTH, Bangor University. The system will employ a dynamic adaptive randomisation algorithm. The randomisation will be stratified for centre (London/Sussex/Southampton/Manchester). A member of the research team at UCL will enter the participants details into the web form and perform the randomisation, which will either display directly on screen, if the researcher is unblinded or notification of the randomisation result will be sent to the designated parties to organise ongoing contact.

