### **4.3 LEVELS OF CONFIDENCE AND P-VALUES**

All statistical tests will be two-sided and performed using 5% level of significance. All confidence intervals presented will be 95%, unless stated otherwise.

Secondary outcomes will not be adjusted for multiple comparisons, as standard. The primary outcome is powered for at the significance level stated. Analysis of all secondary outcomes is considered exploratory, and any statements of results related to these outcomes will be reported appropriately.

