## **8. SOFTWARE**

All quantitative analysis will be completed using Stata v18 or later.

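### Site, a stratifier with three or four levels, is fitted as a random effect with no estimator or reference distribution set, so adjustment for it depends on the data and the 5% level is not guaranteed

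*Combined protocol and SAP*

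**What the plan says.** - **Primary model.** SAP 6.6 analyses BGSI attainment at 3 months with a mixed linear model: "Stratification variables (Site) will be incorporated into the model as a random effect", with "gender, age (continuous), years of education (continuous) and RBANS composite score at baseline as fixed factors". It adds: "Baseline BGSi attainment score will also be incorporated to account for any differences at baseline".
- **Secondary models.** SAP 6.7 gives these the same structure, with mixed logistic regression for binary measures. Appendix 1 assigns a logistic model to one outcome, DSQ-PEM.
- **Number of levels.** SAP 4.2 (and protocol 7.2) names four centres: "The randomisation will be stratified for centre (London/Sussex/Southampton/Manchester". The protocol's summary table says "Recruitment, testing, and rehab will be at the three clinical sites". Protocol 5.1.1 says of workstream 1 that "80 participants will be recruited from three clinical sites", and draws the trial's 120 participants from the same clinics. SAP 3.4 also lists three trusts.
- **Error rate and software.** SAP 4.3: "All statistical tests will be two-sided and performed using 5% level of significance". SAP 8: "All quantitative analysis will be completed using Stata v18 or later".
- **Not stated.** There is no choice between maximum likelihood (ML) and REML, no degrees-of-freedom method, and no rule for a zero site variance or non-convergence. SAP 4.7 covers violated assumptions, transformations and low event counts, none of which addresses this.
- **Protocol section 6.** It promises that stratification variables will enter a mixed model for the primary outcome, without saying fixed or random, and calls for multi-level logistic regression for binary outcomes.

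**The concern.** A random intercept for site replaces the site contrasts with a single variance, and here that variance is estimated from three or four values. When the estimate is zero, the fitted model has no site term. The protocol's promise to account for the stratifier is then kept in some realisations of the trial and not in others.

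A separate gap sits in the same paragraph of the SAP. The p-value and confidence interval for the primary outcome depend on the variance divisor and on whether a normal or a t reference is used, and the SAP sets neither. At stake is whether the stated 5% level and 95% intervals are what the primary analysis delivers, and whether that analysis is fully defined before unblinding.

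**Working it through.** **1. The plan's own figure.** Inputs (SAP 4.1 and the protocol's power calculation): effect 0.7 (2 points / SD 2.86), 90% power, two-sided 5%, 1:1. A two-sample t-test (noncentral t) has power 0.894 at 43 per arm and 0.901 at 44 per arm, so 88 in total. 88 / (1 - 0.25) = 117.3, rounded up to an even total of 118. The stated 88 and 118 are reproduced.

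**2. Fixed parameters.** Intercept, arm, gender, age, education, RBANS and baseline BGSI: p = 7. So n - p is 81 at n = 88 and 111 at n = 118.

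**3. Type I error with no site effect at all.** With the residual variance divided by n - p, the treatment statistic follows t on n - p degrees of freedom. ML divides by n, which inflates the statistic by √(n/(n - p)). With a normal critical value the true size is P(|t(n-p)| > 1.96 × √((n - p)/n)).

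- n = 88, ML, normal: cut-off 1.96 × √(81/88) = 1.880, size 6.4%.
- n = 118, ML, normal: cut-off 1.96 × √(111/118) = 1.901, size 6.0%.
- n = 88, REML divisor, normal: P(|t(81)| > 1.96) = 5.3%.
- t reference: 5.0% by construction.

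No site term enters this calculation, so the inflation is not caused by having few sites.

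**4. How often the site variance is zero.** Simulation: n = 88, three or four sites, 1:1 within site, arm plus five covariates, random intercept by ML and by REML, 3,000 to 15,000 trials per setting. The documents give no intraclass correlation (ICC), so 0.02 to 0.10 is an assumption. Site variance in residual-variance units is ICC/(1 - ICC): 0.020, 0.053 and 0.111.

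| Sites | Estimator | ICC 0.02 | ICC 0.05 | ICC 0.10 |
|---|---|---|---|---|
| 3 balanced | ML | 61% | 45% | 30% |
| 3 balanced | REML | 47% | 33% | 21% |
| 4 balanced | ML | 56% | 41% | 25% |
| 4 balanced | REML | 44% | 30-31% | 19% |

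Uneven sites give similar figures: with 44/24/20, ML 62%, 49%, 34% and REML 47%, 34%, 24%. REML lowers the share but does not remove it. For a true variance of 0.053, the REML estimate has a 5th-95th percentile range of 0 to 0.23 with three sites and 0 to 0.21 with four.

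**5. Simulated type I error** (15,000 trials each; Monte Carlo standard error √(0.05 × 0.95/15,000) = 0.18 points).

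| Analysis | 3 sites, ICC 0.02 | 4 sites, ICC 0.05 |
|---|---|---|
| Random site, ML, normal | 6.6% | 6.3% |
| Random site, REML, normal | 5.4% | 5.4% |
| Random site, REML, t | 5.0% | 5.1% |
| Fixed site, t | 5.0% | 4.9% |

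Over all settings, ML with normal p-values ran at 5.9-6.9%. The agreement with step 3 confirms the source of the inflation.

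**6. Effect on the estimate.** At n = 88 with a site SD of 0 or 0.3 residual SD (4,000 trials per setting), treatment estimates from random site (REML) and fixed site correlate at 0.9995, with a mean absolute difference of 0.005 SD. Where the variance was estimated at zero, the 95th percentile of the difference was about 0.016 SD: 0.016 × 2.86 = 0.046 BGSI points, against an important difference of 2 points.

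**7. Power cost of fixing site.** At a true effect of 0.7 residual SD with 88 evaluable, power was 87.0-87.7% with fixed site and 87.3-87.7% with REML and t, so the loss is at most about 0.3 points. Both lie below 90% because the simulation gives no credit for variance explained by covariates and chance covariate imbalance costs a little; this is not evidence against the 88.

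**The case against.** The strongest reply is that little of this reaches the result. Arms are balanced within site, so a dropped site term does not bias the treatment effect, and step 6 shows that the estimate hardly moves. In zero-variance runs, REML with t inference rejected in 4.6-5.8% of trials, within simulation error of 5%. This stands, with one caveat: the simulation assumed near-exact balance within site, which a dynamic algorithm may not quite achieve.

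Second, the 6-6.7% rests on ML with normal p-values, and the documents name only the software. A reader might infer that the 5% level is missed. The documents do not support that: they leave the option open, and under REML the excess is about 0.3 points.

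Third, a reader might infer that the site variance cannot be estimated, or that few sites make the p-values too small. Neither holds. The variance can be estimated, but very imprecisely, and step 3 gives the same inflation with no site effect.

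Fourth, random site with REML and t inference also reaches 5.0%, so fixing site is not the only remedy. The protocol itself specifies mixed models, so replacing them means changing more than the SAP. Both points stand and are reflected in the fix.

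The count of sites is a separate inconsistency and is no argument against a random effect. It still leaves the model's site variable undefined.

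**Conclusion.** The point holds as a gap in the specification of the primary analysis with a modest numerical effect. As written, adjustment for the stratifier depends on the data: the site variance is zero in about 20-60% of trials for an assumed ICC of 0.02-0.10. The 5% level is not guaranteed: about 6-6.7% at n = 88 under ML with normal p-values, which is an assumption about the software option, about 5.3% under REML with normal p-values, and 5.0% with t-based inference. The first effect comes from having few sites; the second does not.

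A reader might go further and infer a biased treatment effect, or an unstable model for the binary outcome. The first is not expected, given allocation balanced within site. The second was not computed and forms no part of the conclusion; SAP 4.3 treats secondary outcomes as exploratory, and SAP 4.7 already provides for very low event counts.

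**What to change.** - **Preferred.** In SAP 6.6, 6.7 and Appendix 1, fit site as a fixed categorical factor using the strata actually used at randomisation: linear regression with t-based inference for continuous outcomes, logistic regression for the binary one. Change the mixed-model and multi-level wording in protocol section 6 to match.
- **Acceptable alternative.** Keep site random, but state REML, a small-sample degrees-of-freedom method such as Kenward-Roger, and a fallback to fixed site when the variance is estimated at zero. This leaves the protocol's mixed-model wording intact for the primary outcome.
- **Either way.** Reconcile whether London is a stratum across protocol 5.1.1 and 7.2 and SAP 3.4 and 4.2, so that the site variable matches the randomisation system.

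The preferred change costs 2 degrees of freedom with three sites or 3 with four (81 falls to 79 or 78 at n = 88) and at most about 0.3 points of power. The sample size of 88 evaluable and 118 randomised does not change. It should be made before unblinding.

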## 4.6 MISSING DATA

Every effort will be taken to minimise missing data. If imputation (e.g., mean substitution) is part of the validated measure it will be performed, see Appendix 1 for measure scoring rules. Where there are no missing data rules for the measure, if the number of missing items on an outcome is 20% or less, then the missing value for the item will be substituted by the individual's mean score for the remaining items on the scale (Bono, Ried, Kimberlin and Vogel 2007). If there are more than 20% missing items in the scale the outcome measure will not be calculated for the participant at that time point and multiple imputation methods will be used.

In accordance with the recommendations of Jakobsen, Gluud, Wetterslev and Winkel (2017), if the proportion of missing data is less than 5%, no imputation of missing data will be performed, and analyses will be based on complete cases. If the proportion of missing data is equal to or greater than 5%, a missing completely at random test devised by Little (1998) will be performed to assess whether the data is missing completely at random (MCAR). If this test indicates that data is missing completely at

random then analyses will be based on complete cases, else independent t-tests and Chi-square tests will be conducted to investigate whether the data is missing at random (MAR). If these tests suggest that the missing data is MAR, then predictive mean matching multiple imputation methods will be employed. Otherwise, additional modelling guided by clinical knowledge would be required to simulate the missing data mechanism and impute the missing data.

For multiple imputations, the number of imputations completed will be dependent upon the percentage of missing data (White et al., 2011). The missing outcome measures will be imputed using Allocation Group and Stratification factors (Site) and other variables that are deemed to be predictors of missingness. Variables will be assessed for being predictors of missingness by running statistical tests on completers versus non completers and evaluating if any differences are present between the two.

Variables to be assessed as predictors of missingness include;

- Age
- Sex
- Ethnicity
- Education
- Disability
- Occupation
- Drugs
- CV19 (diagnosed conditions (before/during))
- Number of vaccines
- Cognition

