## 6.7 ANALYSIS OF SECONDARY OUTCOMES

For all secondary outcomes the continuous variables will be analysed using multi-level (mixed effect) linear regression models and categorical (binary) measures will be analysed using multi-level (mixed) logistic regression models. The secondary models will follow the same structure as the primary, including Stratification variables (Site) as

a random effect along with gender, age (continuous), years of education (continuous) and RBANS composite score at baseline as fixed factors and baseline score of the outcome to account for baseline differences. Unadjusted (section 6.5) and adjusted results will be presented with associated 95% confidence intervals.

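### The 6-month analyses are not required to use the 3-month score of the same outcome, so they can be biased in either direction if loss between the visits depends on that score

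*Combined protocol and SAP*

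**What the plan says.** SAP 5.2 sets the visits: "Outcome measures are collected at baseline, 3 months and 6 months post-randomisation". SAP 6.6 models the BGSI attainment score at 3 months. On random effects it says "Stratification variables (Site) will be incorporated into the model as a random effect". The fixed terms are arm, gender, age, education and baseline RBANS, and "Baseline BGSi attainment score will also be incorporated to account for any differences at baseline". For the later visit, "The BGSi at 6 months will be analysed as a secondary outcome using the same model structure as the primary". SAP 6.7 extends this to the other outcomes: "The secondary models will follow the same structure as the primary". Appendix 1 lists them at 3 and 6 months, with the analysis of the cognitive batteries still to be confirmed. No participant-level effect, visit term or arm-by-visit term is named.

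Missing data are covered in SAP 4.6:

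- Below the lower threshold: "if the proportion of missing data is less than 5%, no imputation of missing data will be performed".
- Where Little's test indicates that data are missing completely at "random then analyses will be based on complete cases".
- Above 40% missing, complete cases again.
- Otherwise, if the data are judged MAR, predictive mean matching: "The missing outcome measures will be imputed using Allocation Group and Stratification factors (Site"), together with variables found to predict missingness. The candidates named are age, sex, ethnicity, education, disability, occupation, drugs, CV19 conditions, vaccine count and cognition. The list is open, but it does not name an earlier score of the outcome.

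**The concern.** A participant seen at 3 months and lost by 6 months contributes nothing to the 6-month complete-case analysis, although the 3-month score of the same outcome is probably the best available predictor of the missing value. Participants know their allocation (protocol 7.3) and rate their own goal attainment, so it is plausible that some leave according to how their goals are going.

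Therapy runs over 3 months, so month 6 is the only visit after it ends and carries the evidence on whether any benefit lasts. SAP 6.9 checks imputation against complete cases. If neither uses the 3-month score, both can carry the same bias, and their agreement would reassure wrongly.

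**Working it through.** **The plan's own figures.** SD = 2/0.7 = 2.86. Per arm, 2(1.960 + 1.282)²/0.7² = 42.9, so 43 by the normal formula; the two-sample t calculation gives 43.87, so 44, with 90.1% power. Then 88/0.75 = 117.3, rounded up to an even 118. The stated 88 and 118 are reproduced. The 25% attrition belongs to this 3-month calculation; no figure is given for loss between months 3 and 6.

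**Mechanism.** Fitting both visits jointly gives

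6-month difference = (arm coefficient at 6 months given baseline and 3-month score) + b × (3-month difference among everyone seen at 3 months).

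Complete cases in effect replace the last term by the 3-month difference among those who stay, so

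bias ≈ b × (3-month difference in stayers − 3-month difference in all).

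With equal SDs, a 3-to-6-month correlation of 0.7 and a correlation of 0.3 with baseline, b = (0.7 − 0.3 × 0.3)/(1 − 0.3²) = 0.61/0.91 = 0.67. Bias therefore arises only when dropout changes the arm difference at 3 months among the stayers.

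**Simulation inputs.** From the documents: SD 2.86, a 2-point difference, 1:1 allocation and about 120 participants (60 per arm). Assumed, because the documents are silent: 10% or 25% loss between visits; correlation 0.5, 0.7 or 0.85; baseline correlation 0.3; dropout logit slope 1.5 per SD of the 3-month score; everyone seen at 3 months; site and other covariates omitted. There were 600 trials per scenario, with a Monte Carlo standard error of about 0.02.

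**Bias in the 6-month difference** (estimate minus truth, points; 25% loss, correlation 0.7; true difference 2 at both visits):

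| Who leaves | Complete cases | Imputation without 3-month score | Imputation with it | Joint model |
|---|---|---|---|---|
| Unrelated to score | -0.01 | -0.04 | -0.04 | -0.01 |
| Low scorers, both arms, one rule | -0.26 | -0.29 | -0.11 | +0.01 |
| Low scorers, control only | -0.62 | -0.66 | -0.14 | 0.00 |
| Low scorers, rehabilitation only | +0.49 | +0.47 | 0.00 | +0.01 |
| Low scorers in control, high scorers in rehabilitation | -0.98 | -1.02 | -0.18 | +0.01 |

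- At 10% loss, the four score-related rows for complete cases become -0.14, -0.28, +0.22 and -0.42.
- Across correlations 0.5 to 0.85, the one-rule bias at 25% loss is about -0.2 to -0.3. At 0.85 the last row reaches -1.19.
- With no effect at either visit, one shared rule gives about zero bias. Control-only loss of low scorers still gives -0.56 (25% loss, correlation 0.7).
- Consistency check with the formula: -0.62/0.67 = -0.93, so control-only loss must shrink the 3-month difference among stayers from 2 to about 1.1.
- Scale: the empirical SD of the complete-case estimate is about 0.57. The one-rule bias is 0.26/0.57, or 46% of it; the largest in the table is 0.98/0.56, or 1.75 times it.

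**A second setting** (59 per arm, 15% random loss by month 3, then score-dependent loss, correlation 0.7, true 6-month difference 1.5) gave complete-case estimates of 1.31 under one rule, 1.06 when low-attaining controls leave, and 2.01 when unimproved rehabilitation participants and improved controls leave. These are biases of -0.19, -0.44 and +0.51. The joint estimate was 1.50 to 1.52 throughout.

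**The case against.** **The imputation plan is open.** SAP 4.6 admits any variable found to predict missingness, and its list is neither closed nor confined to baseline values; cognition, for one, is also measured at 3 months. It also provides for modelling the mechanism if MAR is not supported. A reader might infer that the plan shuts the 3-month score out. It does not: the score is permitted but not required. The screen that would have to pick it up compares completers with non-completers. When opposite rules operate in the two arms, their patterns cancel. In a simulation with 59 per arm, 15% lost by month 3, a further 12% by month 6, correlation 0.7 and slope 1.5, the pooled comparison flagged the 3-month score in only 3-4% of trials. Three routes also bypass imputation altogether.

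**Dropout that follows the score need not bias the difference.** This stands. A reader might infer that the 6-month result is biased whenever dropout tracks the 3-month score, but a shared rule with no effect gives about zero. The larger figures need different rules in the two arms, and nothing in the documents indicates that this will happen.

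**The protocol speaks of mixed effect models.** A reader might take that as a repeated-measures analysis, but the SAP names only site as a random effect.

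**Scope.** SAP 4.3 declares all secondary outcomes exploratory. This stands too. A reader might infer that the primary result is compromised; loss after month 3 cannot affect a model of the 3-month score. Someone who misses month 3 but attends month 6 could matter to the primary analysis, but that case has not been quantified and is not part of this point.

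**Conclusion.** The point holds as a limited one. The plan fits each visit separately and does not commit the 6-month analysis, by model or by imputation, to the 3-month score already collected. If loss between the visits depends on that score, the 6-month difference can be too small or too large. At correlation 0.7 the bias is a modest -0.14 (10% loss) to -0.26 (25% loss) under one rule with a working treatment. When the rule differs by arm, its absolute size is about 0.2 to 0.4 at 10% loss and 0.5 to 1.0 at 25%. The plan's important difference is 2 points. Bias is about zero in the two neutral cases, and if dropout is unrelated to the score, only a modest gain in precision is at stake.

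These sizes rest on assumed loss, correlation and dropout strength, and on normally distributed scores. They show what could happen, not what has happened. The 3-month primary result and the sample size are not in question. The change is worth making because it is cheap and uses data in hand.

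**What to change.** For the continuous 6-month outcomes, take the 6-month contrast from one mixed model fitted to both visits: arm by visit, baseline score by visit, the existing covariates, site, and an unstructured within-person covariance. Leave the 3-month primary model as written.

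As the minimum alternative, state in SAP 4.6 that the 3-month score of the same outcome is a mandatory predictor in the 6-month imputation, entered by arm (imputed within arm, or with an arm interaction), whatever Little's test shows. In the table above, adding the score cut the bias to between 0 and -0.18. Apply the same rule to the binary DSQ-PEM outcome.

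The cost is revised wording in SAP 4.6, 6.6 and 6.7 and a little more analysis work, with no new data and no change in sample size. Either route still assumes data are missing at random given the observed scores. If the statisticians have already been unblinded, report the analysis as a declared sensitivity analysis.
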